### Secondary outcome measures

To measure participants’ self-reported smoking status women will complete one baseline and eight follow-up self-report touchscreen computer surveys. The computer survey was programed using Digivey survey software
[23]. Use of computer surveys to assess smoking status has been shown to be a reliable and accurate method of data collection
[24], as well as being reported as enjoyable and easy to complete by most participants
[22].Questions assessing participants’ demographic characteristics and factors previously found to be associated with smoking status will also be included. The following questions will be included in the self-report, touchscreen computer surveys:

*Baseline survey*:

• *Smoking status and history* will be assessed through standardised questions or questions adapted from previous research
[22,25-32] with many items based on the previous the work of Bryant et al.
[22,26,27] Items will include: current smoking status
[22,26], number of cigarettes currently smoked per day
[30], smoking history, previous quit attempts, reductions in smoking
[25,26], strategies used to assist in previous quit attempts
[26,27], readiness/stages of change
[29,31], financial stress
[33,34], whether they smoked during any previous pregnancies
[32]and whether they attempted to quit or reduced smoking during any previous pregnancies
[26,32]. Questions assessing women’s exposure to environmental smoke will also be included
[25,26,32].

• *Demographic characteristics*: women will be asked to answer questions relating to their: age, date of birth, highest level of education, Aboriginal or Torres Strait Islander status, current household income, marital status, number of previous pregnancies, gestation period, postcode, number of adults and children (<18 years) residing in their household.

• *The Patient Health Questionnaire**2* (*PHQ2*)
[35]: Will be included as a short, simple measure of participants’ levels of depression. The PHQ2 consists of two questions, which assess respondent’s level of depressed mood in the previous 2 weeks
[35]. Respondents rate the frequency of depressed mood and anhedonia on a four point likert scale, ranging from 0 (“not at all”) to 3 (“nearly every day”)
[35]. Total score on the PHQ2 range from 0 to 6. A score of 4 has recommended as an appropriate cut-point for screening for possible depressed mood in pregnant women
[36]. The PHQ-2 has evidence of criterion validity; as well as acceptable specificity (92%) and sensitivity (83%)
[35]. Previous research has found a relationship between depression and smoking status
[37,38].

• *Economic questions*: Women will be asked to a number of questions relating to their personal out-of-pocket costs, time costs and health care utilisation incurred as a result of the intervention.

• *Social characteristics*: women will be asked whether their partner or others within their household smoke.

*Follow*-*up surveys*: During each of the follow-up visits, women will be asked to complete a brief touchscreen computer survey using a number of items from the baseline survey. Questions will assess their current smoking status, number of cigarettes smoked per day (if they have not abstained), changes in smoking behaviour, partners’ current smoking status, exposure to environmental smoke, the number of quit attempts made, gestation age; the PHQ2 and efforts to engage with quit smoking support services.

The following two biochemical analyses will be used to validate women’s self-reported smoking status:

1. *Saliva cotinine analysis*: will be used to biochemically validate self-reported smoking status for all participants at baseline and each of the eight intervention sessions using the NicAlert® semiquantitative dipstick assay. A previous study analysing 167 family practice patients using NicAlert® illustrated acceptable levels of sensitivity (99%) and specificity (96%)
[11].Cotinine analysis with the NicAlert® dipstick takes approximately 20 minutes and can be performed by untrained persons, highlighting the potential utility of such a test in clinical practice .

2. *Hair cotinine analysis*: will be undertaken during the eighth or final intervention session. Participants will be asked to provide a small sample of hair taken from the nape of the neck. Samples will be transported to an off-site laboratory for analysis. Hair cotinine analysis can reliably quantify long-term exposure to tobacco, with each centimetre of scalp hair representing approximately 1 month of past exposure
[39]. Gas chromatography – mass spectrometry will be used to analyse hair cotinine levels, as it is considered the standard reference in analysis of cotinine
[40]. A cut-point of 0.2 ng/mg has been found to distinguish between pregnant active smokers and passive or unexposed with high levels of sensitivity (91%), specificity (94%) and test accuracy (91.7%)
[40]. We will also validate hair cotinine analysis as a measure of smoking status by comparing its accuracy against women’s self-report smoking status and saliva cotinine throughout the study.

#### Economic outcomes measures

The feasibility of undertaking a cost-effectiveness analysis will also be undertaken. This will include the collection of data on the costs of the interventions that would include the amount of money received by each participant, and the costs of administering the payments in terms of staff time and other resources used. The intervention may also encourage patients to attend their antenatal visits, and potentially other health care visits associated with their pregnancy, more often than the control group, and so data will also be collected on patients’ utilisation of health services throughout the study. The feasibility of obtaining these data from Medicare, PBS, and hospital separations data, including obtaining patients’ consent, will be investigated and compared to gathering this data directly from patients using a standard questionnaire administered at each visit. The costs incurred by patients are also likely to be affected by the intervention. This will include savings in purchasing cigarettes, and differences in out of pocket, travel and time costs of attending if the intervention influences health care utilisation. These data will be collected from a short patient survey administered at each visit. Out of pocket costs for GP visits and prescribed medication can also be collected from MBS and PBS records. The effectiveness data on quitting will be collected as mentioned above, and combined with the data on costs. Incremental cost-effectiveness ratios (ICERs) will be calculated
[41].

### Sample size

A convenience sample size totalling 90 women will be recruited, with 30 women randomised to each of the three study groups. As this is a proof-of-concept trial, the sample size will not be adequately powered to detected small differences however a sample size of 30 women in each group will allow for detection of a difference in smoking rates between groups of 24%, with 5% significance level and 68% power. Based on previous studies, this will be sufficient to provide an estimate of the difference in proportions between groups for the following primary outcomes: (i) consent rates; (ii) lost to follow-up rates; (iii) participant compliance to saliva and hair cotinine analysis; (iv) acceptability of incentives and validation measures, and the secondary outcome variable, smoking cessation. To allow for a 20% drop-out rate, a consent rate of 60% and 10% of women being ineligible, 208 pregnant women who smoke will be approached. Based on a previous study conducted by the investigators, approximately 17% of women seen at this clinic are self-reported smokers
[21].

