**Method:**

Ninety (90) pregnant women who self-report smoking in the last 7 days and whose smoking status is biochemically verified, will be block randomised into one of three groups: a. No incentive control group (n=30), b. $20 incremental incentive group (n=30), and c. $40 incremental incentive group (n=30). Smoking status will be assessed via a self-report computer based survey in nine study sessions with saliva cotinine analysis used as biochemical validation. Women in the two incentive groups will be eligible to receive a cash reward at each of eight measurement points during pregnancy if 7-day smoking cessation is achieved. Cash rewards will increase incrementally for each period of smoking abstinence.

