### Participants

A sample of ninety (90) consenting pregnant women will be recruited to participate. Women will be considered eligible if they are: (1) aged at least 16 years; (2) presenting for their first antenatal visit; (3) less than 31 weeks gestation; (4) sufficient in English language to complete the survey; and (5) a current smoker (defined as having smoked in last 7 days and a return a positive saliva sample for cotinine). Pregnant women will be ineligible to participate if they have elected to receive shared antenatal care with their GP and/or are considered by clinic staff to have a severe cognitive or psychiatric disorder; currently being treated for chemical dependency other than alcohol or tobacco; or have quit smoking before their first antenatal appointment.

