### Secondary outcomes

#### Quit rates

Although not adequately powered for detecting small differences in the secondary outcomes, Fisher’s exact test will be used to detect potential differences in smoking cessation rates between groups and to demonstrate potential effectiveness of the intervention. Differences between experimental groups in the secondary outcome - PHQ2 will be assessed using the Kruskal-Wallis test. Fisher’s exact tests will be used to compare conditions on post-partum smoking rates at 6 weeks after delivery.

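### The sample-size paragraph uses 90 both as women randomised and, through the 208 to be approached, as women completing; the 68% power needs 30 analysed per arm and omits the control quit rate and sidedness

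*Protocol article*

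**What the plan says.** All references are to the Protocol article.

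- Sample size fixes the size of the trial: "A convenience sample size totalling 90 women will be recruited, with 30 women randomised to each of the three study groups". Participants agrees ("A sample of ninety (90) consenting pregnant women will be recruited to participate"), and so does the Method paragraph of the Abstract ("will be block randomised into one of three groups: a. No incentive control group (n=30", with 30 in each incentive group as well). In all three places 90 is the number entering the trial.
- Sample size then gives the only power statement: 30 per group will "allow for detection of a difference in smoking rates between groups of 24%, with 5% significance level and 68% power". It names no control quit rate, no sidedness and no test for this calculation.
- It next allows for 20% drop-out, together with "a consent rate of 60% and 10% of women being ineligible, 208 pregnant women who smoke will be approached".
- Quit rates names the test for cessation: Fisher's "exact test will be used to detect potential differences in smoking cessation rates between groups". Primary outcomes, under Analysis, names the same test and puts the emphasis on 95% confidence intervals rather than p-values.

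**The concern.** Two things do not fit together.

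First, a drop-out allowance raises the number to be randomised so that the target remains at the end. If 90 is the number randomised, drop-out has no place in working out how many women to approach. If 90 is the number remaining, more than 90 must be randomised. The section does both. This affects the recruitment target, the number approached and the number analysed. Consent and loss to follow-up are primary outcomes here, so the number expected to enter should be clear.

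Second, the power of a comparison of two proportions depends on where the proportions lie as well as on their difference. A 24-point difference without a control rate does not determine a power. The method that most simply gives 68% is also not the planned test. A reader of a null cessation result would take the stated two-in-three chance of detection at face value.

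**Working it through.** **Inputs from the protocol:** 90 women in three arms of 30; 24-point difference; 5% level; 68% power; Fisher's exact test; 20% drop-out; 60% consent; 10% ineligible; 208 approached.

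**Assumed, because not stated:** the control quit rate (shown over a range) and a two-sided test (one-sided also shown). Women are treated as independent. It makes no difference whether the 24 points are read as smoking or as quitting, since 6% v 30% quitting is 94% v 70% smoking.

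**1. The approach number**

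- Reproducing the plan's figure: 90 / (0.9 x 0.6 x 0.8) = 208.3, which gives the 208.
- Forwards: 208 x 0.9 = 187 eligible; x 0.6 = 112 consenting and randomised (about 37 per arm); x 0.8 = 90 completing (30 per arm).
- If 90 are randomised: 90 / (0.9 x 0.6) = 167 approached; 90 x 0.8 = 72 completing (24 per arm).

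The two meanings differ by 22 women randomised (112 v 90) and 41 approached (208 v 167).

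**2. The 68%**

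Pooled two-sided normal approximation, n per arm:

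power = Φ{ [|p2 − p1| − 1.96 √(2p̄(1−p̄)/n)] / √([p1(1−p1) + p2(1−p2)]/n) }

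With p1 = 0.06, p2 = 0.30, p̄ = 0.18, n = 30:

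- 1.96 x √(2 x 0.18 x 0.82/30) = 1.96 x 0.0992 = 0.1944
- √((0.0564 + 0.2100)/30) = 0.0942
- (0.24 − 0.1944)/0.0942 = 0.484, and Φ(0.484) = 0.686

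So the plan's figure fits this approximation at about 6% v 30%.

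**3. The planned test**

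Exact Fisher power is the sum, over all pairs of quit counts (a, b) whose Fisher p-value is at most 0.05, of Bin(a; n, p1) x Bin(b; n, p2). For a 24-point difference:

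| Control v incentive quit rate | Normal approx., n=30 | Fisher two-sided, n=30 | Fisher one-sided, n=30 | Fisher two-sided, n=24 |
|---|---|---|---|---|
| 0% v 24% | 83.4% | 76.0% | 87.9% | 71.7% |
| 1% v 25% | 80.5% | 71.0% | 83.0% | 66.9% |
| 2% v 26% | 77.8% | 67.2% | 79.3% | 62.8% |
| 5% v 29% | 70.6% | 59.4% | 71.4% | 52.9% |
| 6% v 30% | 68.6% | 57.5% | 69.3% | 50.3% |
| 7% v 31% | 66.6% | 55.7% | 67.4% | 48.1% |
| 10% v 34% | 61.7% | 51.1% | 62.8% | 42.8% |
| 20% v 44% | 51.3% | 41.3% | 54.1% | 33.0% |

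Two-sided Fisher with 30 per arm equals 68.0% at 1.75% v 25.75%. With 24 per arm it reaches 68% only below 1% control quitting. The loss from 30 to 24 per arm does not depend on the choice of test: the normal approximation at 6% v 30% also falls, from 68.6% to 58.5%.

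**The case against.** The strongest reply concerns the power figure. A reader might infer from the table that 68% is wrong and that the true chance of detection is near one half. The documents do not support that. They give no control quit rate, so 5-10% is an assumption made here. Two-sided Fisher gives 68% or more when control quitting is about 1.75% or lower, and one-sided Fisher gives 67-69% at 6-7%. A journal article may also leave the control rate and the method to a fuller document. This stands: with 30 analysed per arm, 68% is unverifiable as written rather than disproved.

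A reader might also infer that 208 is miscalculated. It is not; the conflict lies in what 90 means. Approaching 208 would over-supply, not under-supply, 90 recruits.

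Finally, the stakes are limited. The trial is declared proof-of-concept with a convenience sample, cessation is a secondary outcome, low power for small differences is conceded twice, and the emphasis is on confidence intervals. This also stands, and it lowers the weight of the point. It does not remove the conflict between 90 and 112, which uses only the article's own figures. The caveat about small differences does not cover a stated power for a 24-point difference, and p-values will still be reported.

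**Conclusion.** The recruitment conflict is established without any outside assumption. If 90 are completers, then 208 approached and 30 analysed per arm agree with each other, but about 112 must be randomised, against the three statements that 90 enter. If 90 are randomised, 208 is 41 more than needed, and the article's own 20% drop-out leaves 24 per arm if only completers are analysed, fewer than the 30 behind the 68%.

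The power finding is conditional. The 68% cannot be reproduced without a control rate and sidedness. It matches a two-sided normal approximation at about 6% v 30%, where two-sided Fisher gives 57.5%. If control quitting is 5-10% and the test is two-sided, Fisher power is 59-51% with 30 per arm and 53-43% with 24.

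Moderate: the figures should be made consistent, but no primary outcome analysis depends on the 68%.

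**What to change.** In Sample size:

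1. Say whether 90 is the number randomised or the number completing, and make the approach number agree. For 90 randomised: 167 approached. For 90 completing: 208 approached and about 112 randomised, with the Abstract and Participants changed to match.
2. Restate the power for the planned Fisher test at the number analysed, naming the assumed control quit rate and the sidedness. For example, two-sided with 30 analysed per arm: 57.5% for 6% v 30% and 51% for 10% v 34%. If 90 are randomised and only completers are analysed, use 24 per arm: 50% and 43% for the same rates. If all 90 randomised women are analysed, say so; 30 per arm then stands and no drop-out allowance is needed.

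The cost is rewording and, at control rates above about 2% with a two-sided test, a less favourable stated power. The completers reading means 22 more women randomised than the 90 now stated, but the 208 already implies them.

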### Analysis

Baseline demographic and social characteristics of patients in all the three treatment groups will be summarised separately. Continuous data will be expressed as mean values with standard deviations (SD), and categorical data will be presented as counts with percentages.

### Primary outcomes

Proportions and frequencies will be calculated to assess the following outcomes: (i) participant consent rates; (ii) loss to follow-up rates; and (iii) participant compliance with saliva and hair cotinine analysis. Proportions and frequencies will also be calculated for all closed-ended questions included in the study participant and clinic staff interviews to allow investigation of: (iv) participant acceptability of touchscreen computers for self-reported smoking rates and demographics; and (v) acceptability of incentives to staff and study participants. Differences between experimental groups in the proportion of each of these five primary outcomes and the secondary outcome (proportion quit smoking) will be assessed through Fisher’s exact test. Differences between participant subgroups and these outcomes will also be assessed using Fisher’s exact test. Although p-values from the above will be reported, the focus will be on providing 95% confidence intervals around point estimates for comparisons of all three treatment arms.

Qualitative analysis will be performed on open-ended questions included in participant and staff interviews investigating the following primary outcomes: (vi) acceptability of saliva and hair cotinine analyses for biochemical validation of smoking status; and (vii) perceived barriers and facilitators to using financial incentives. All interviews will be transcribed verbatim and a thematic analysis will be performed independently by two of the research team members.

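### The Fisher tests of participant subgroups against quitting and acceptability of incentives have no term for arm, so they cannot show whether the incentive effect differs between subgroups

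*Protocol article*

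**What the plan says.** The Primary outcomes part of the analysis section first compares the three arms by Fisher's exact test on "each of these five primary outcomes and the secondary outcome (proportion quit smoking"), six outcomes in all. The next sentence carries the same test over to subgroups: "Differences between participant subgroups and these outcomes will also be assessed using" Fisher's exact test. No arm term, stratification or within-arm comparison is mentioned.

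On reporting, the section says that p-values will be given but that "the focus will be on providing 95% confidence intervals around point estimates for comparisons of all three treatment arms". That emphasis on estimation is worded for comparisons between arms; nothing similar is said for subgroups.

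No subgroup is named. The section on secondary outcome measures says that demographic questions and "factors previously found to be associated with smoking status will also be included" in the surveys. These are possible subgroup factors, but none is designated as one.

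**The concern.** The incentive is meant to change quitting, and the amount offered may well change how acceptable women find incentives. For these two outcomes the arm is part of the explanation, and a two-way table of subgroup by outcome leaves it out. A difference in such a table can arise because one subgroup quits more readily whatever it is offered, because one subgroup happens to contain more women from the incentive arms, or because the incentive works differently. The test does not separate the three. Uneven arm make-up is possible because the Randomization section allocates by day and session of the first visit, and subgroups may differ in when they attend.

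At stake is what a later, larger trial takes from this pilot. A significant subgroup result for quitting could be read as guidance on whom to offer incentives to, and the stated method cannot carry that reading. A real difference in incentive effect could also go unseen.

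**Working it through.** **1. The plan's own figure.** The plan gives no power or error rate for the subgroup tests. The nearest figure is the power to allow "detection of a difference in smoking rates between groups of 24"% "with 5% significance level and 68% power", "with 30 women randomised to each of the three study groups". No control quit rate is stated, so one must be assumed. With the pooled two-sided normal approximation,

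power = Φ{[0.24 − 1.96·√(2p̄(1−p̄)/30)] / √(p₁(1−p₁)/30 + p₂(1−p₂)/30)}.

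At an assumed p₁ = 0.06, p₂ = 0.30 and p̄ = 0.18, this is Φ{(0.24 − 1.96 × 0.0992)/0.0942} = Φ(0.48) = 68.6%. At 5% control quitting it is 70.6%, at 8% 64.9% and at 10% 61.7%. So 68% is attainable, but it concerns two full arms of 30 and not subgroups.

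**2. What the pooled subgroup test compares.** Let p(g,j) be the quit rate of subgroup g in arm j, and w(g,j) the share of subgroup g that is in arm j. The test compares Q(g) = Σⱼ w(g,j)·p(g,j) between subgroups. The incentive effect in subgroup g is D(g) = quit rate in the incentive arms minus quit rate in control. Q can differ while D is the same, and D can differ while Q is the same.

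**3. Simulation.** Assumptions: two subgroups of 45, 15 women in each arm-by-subgroup cell, two-sided Fisher test at 5%, 20,000 trials per row. Quit rates are assumed and listed as control / $20 / $40.

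| Scenario | Subgroup A (%) | Subgroup B (%) | Q(A), Q(B) | D(A), D(B) | Significant |
|---|---|---|---|---|---|
| Factor predicts quitting, no incentive effect | 5 / 5 / 5 | 30 / 30 / 30 | 5, 30 | 0, 0 | 86.6% |
| Factor predicts quitting, same incentive effect | 5 / 29 / 29 | 25 / 49 / 49 | 21, 41 | +24, +24 | 45.4% |
| Crossover of incentive effect | 5 / 29 / 29 | 29 / 17 / 17 | 21, 21 | +24, −12 | 2.2% |
| No subgroup difference | 10 / 34 / 34 | 10 / 34 / 34 | 26, 26 | +24, +24 | 2.0% |

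In the crossover row both pooled rates are 63/3 = 21%, although the incentive effects differ by 36 points. The gap between 2.2% and 2.0% (0.0221 − 0.0203 = 0.0018) is within simulation error: each standard error is about √(0.02 × 0.98/20,000) = 0.001, or about 0.0014 for the difference.

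The crossover was chosen so that the pooled rates coincide. A milder interaction would show up in part: 5 / 29 / 29 against 5 / 5 / 5 gives pooled rates of 21% and 5%. But a purely prognostic factor with quit rates of 21% and 5% in every arm gives the same two pooled rates, and the test cannot tell the two apart. The equal cells also rule out uneven arm make-up, so that source of error comes on top.

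**4. Chance findings.** With k factors and six outcomes there are 6k tests. The expected number of false positives is 6k·α; the chance of at least one, if the tests are independent, is 1 − (1 − α)^(6k).

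- k = 3, α = 0.05: 18 × 0.05 = 0.9 expected; 60% chance of at least one.
- k = 10, α = 0.05: 60 × 0.05 = 3.0 expected; 95% chance of at least one.

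Fisher's actual size at n = 90 is lower: 0.6% to 3.0% for a 45/45 split and 2.3% to 4.4% for 30/60, over assumed outcome rates from 5% to 90%. At 2% to 3%, the expected counts fall to 0.36–0.54 for k = 3 and 1.2–1.8 for k = 10. Since k is not given, no single count follows from the plan.

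**5. What a comparison of incentive effects could deliver.** For one incentive arm against control, 15 women per cell, an effect of 24 points in one subgroup and none in the other, and 5% control quitting, the standard error of the difference in effects is √[(3 × 0.05 × 0.95 + 0.29 × 0.71)/15] = 0.152. Power is Φ(0.24/0.152 − 1.96) = 35%. With 10% control quitting it is 26%. Within one subgroup, the 95% CI for a 5% against 29% comparison has a half-width of about 1.96 × √[(0.05 × 0.95 + 0.29 × 0.71)/15] = 0.25, by the normal approximation, which is rough with cells this small.

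**The case against.** A reader might infer that the plan intends these tests to show for whom incentives work. It does not say so. The primary aim is feasibility, and neither the aims nor the analysis section claims to look for differential benefit.

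Nor is the missing arm term a defect for all six outcomes. Whether consent, loss to follow-up, sample compliance or touchscreen acceptability varies with participant characteristics is a proper feasibility question, and a marginal test addresses it. For consent an arm term hardly matters, because the Procedures section places written consent before the incentive scheme is explained.

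A reader might also infer that the tests would produce several chance findings. That depends on how many subgroups are tested, which the article does not state; naming, limiting and labelling subgroups is detail that an article may leave to the fuller plan. The survey items are not designated as subgroups, some overlap (age and date of birth), and they do not exist for women who decline, since the baseline survey follows consent.

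The wording does not exclude running the tests within each arm. That would remove the pooling, but it would still not compare incentive effects between subgroups.

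Finally, a subgroup difference stratified by arm is itself an average association and does not show effect modification. That is correct, and it is why the fix also asks for arm differences within subgroups.

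These objections narrow the point to quitting and acceptability of incentives. They do not answer it there: the test is a stated choice of method, and it lacks a term for arm.

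**Conclusion.** The point holds for the proportion quit and for acceptability of incentives, and it is minor. As written, the subgroup test can be significant in most trials (about 87%) for a factor unrelated to any incentive effect, and in only about 2% when the incentive effect truly crosses over. These figures rest on assumed quit rates and 15 women per cell; the simulation covered quitting only. For acceptability of incentives the argument rests on the same missing arm term.

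The documents do not support saying that the tests will yield several false positives, that they are wrong for the other four outcomes, or that the plan misrepresents their purpose. Chance findings could arise: at nominal 5%, 0.9 expected for three factors and 3.0 for ten, and fewer at Fisher's actual size.

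**What to change.** For quitting and for acceptability of incentives, replace the pooled subgroup Fisher test with the subgroup difference stratified over the three arms (Mantel-Haenszel), with a 95% CI. For quitting, also show the difference between arms within each subgroup, with a 95% CI. State that both are exploratory and that the stratified subgroup difference is not evidence of differential benefit. The marginal tests for the other four outcomes can stay.

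This takes a sentence or two in the analysis section, uses data already planned, and extends to subgroups the estimation focus that the section already sets for arms. The cost is slightly more analysis and wide intervals, about ±25 points in the example above. A formal interaction test would add little at 26% to 35% power, so intervals are the realistic output.
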